#### Peer support via social media

Participants in group C will be invited to join a Facebook closed-group. The aim of this group is to provide a platform for participants to share their experiences, ask for advice, support or motivation from peers, and discuss technical or practical challenges. The project team, as administrators, will provide general information and educational advice about PA, motivational support, rewarding messages, technical and practical help. This, in turn, might prevent dropouts.

### Recruitment and study procedures

Potential participants will be invited primarily *via* Facebook advertised campaigns designed to address adults who fit the inclusion criteria (Figure 2). Advertisement through local newspapers will also be used. People will express their interest, complete an online form including questions on the eligibility criteria (answers will be self-reported), and sign an electronic informed consent. Eligible participants will receive information about the study by e-mail and have a discussion with the research team if needed.

**Figure 2 F2:**
[figure not shown]
Flow of study participants.

At enrolment, participants will receive the ActiGraph GT3X+ accelerometer by mail, asked to wear it for eight consecutive days and return it by a prepaid mail envelope. Participants will also be asked to measure their waist circumference and complete the online study questionnaires. Participants will then be randomized to one of the three groups and be informed about which group they have been assigned to.

After enrolment, all participants will receive the activity tracker Mi Smart Band 5 directly to their homes and install the PAI Health app on their smartphone. Detailed instructions on how to use the activity tracker and the PAI Health app will be sent to each participant by email, together with together with a 6-week acclimatization programme. Participants in groups B and C will receive personal credentials to access to Les Mills+. Participants in group C will be invited to a Facebook group used for peer support.

At 6-, 12-, and 18-month participants will undergo a follow-up, asked to wear the ActiGraph GT3X+ accelerometer for eight consecutive days, measure their waist circumference, and complete the online study questionnaires. Qualitative interviews will be conducted in a subsample of participants (*n* = 18–20) at 6- and 18-month to explore their perception of the implementation of the interventions. During data collection, participants will be encouraged to continue participating in the study. A gift card (NOK 300) will be sent to each participant after completion of the 6-month follow up to prevent attrition. Data collection for all follow-ups will be performed remotely, as no clinical examinations are planned at any time point. Study end is set 18 months after enrolment.

### Study objectives and hypotheses

The primary objective of this study is to test which combination of digital interventions is more effective in increasing PA levels among physically inactive adults and sustaining long-term exercise adherence. The secondary objective is to determine the effects on health and implementation outcomes, including: proportion of participants reaching PA recommendations; exercise adherence; physical fitness; cardiovascular risk; quality of life; perceived competence for exercise; self-efficacy; social support; usability; users' perspectives on implementation outcomes (adoption, acceptability, adherence, sustainability).

We hypothesize that the use of activity trackers with the personalized metric PAI can promote PA and improve health outcomes. Furthermore, we hypothesize that the additional use of home-based online training is more effective in engaging in regular PA. Finally, we hypothesize that participation in peer support group *via* social media will result in better long-term adherence to PA.

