### Description of the interventions

#### Activity tracker With PAI app

Participants in groups A, B and C will be provided with an activity tracker (Mi Smart Band 5, Xiaomi, China) and use the personalized metric PAI through an app (PAI Health, Canada). PAI is a personalized metric based on robust epidemiological evidence which links personalized data to an individual's health (16, 18). PAI takes into account age, sex, resting and maximum heart rate, and analyses a continuous stream of heart rate data acquired from the user to provide a single score indicating whether the current PA level is sufficient to obtain or sustain good health (16). A score of ≥100 weekly PAI has been shown to reduce the risk of premature death due to cardiovascular disease in healthy adults as well as individuals with known risk factors, regardless of whether or not the current PA recommendations were met (18). Moreover, a PAI score ≥100 at baseline, maintaining ≥100 PAIs and an increasing PAI score over time was associated with lower mortality risk (35). Heart rate and accelerometery data are recorded and stored automatically on a daily basis, and an individual feedback on the current PAI score is provided through the smartphone app. This also works as a reminder to keep a weekly PAI score above 100 for disease prevention and health promotion.

All participants will also receive information on recommendations for PA, together with a 6-week acclimatization programme consisting of aerobic activity (two times per week) and muscle-strengthening (one time per week). For aerobic activity, information will be provided on how to exercise in moderate intensity (participants begin to sweat but can speak) including warm up, duration and intensity, examples of activities (e.g., jogging, running, cycling, cross-country skiing, swimming, ball sports, martial arts) and how to make progress in the programme. Participants will be also introduced to high-intensity (hard effort, participants cannot speak) interval training with an example of a 4 × 4 program consisting of four bouts of 4-min high-intensity training and 3-min cool-down. For muscle-strengthening, participants will be provided with an example of programme consisting of five exercises (for legs, back, arms and shoulders) be performed with four sets of four repetitions, and instructed on how to perform each exercise (description and link to a video) and make progress by increasing load.

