### Statistical analysis

Descriptive statistics will be reported as mean and standard deviation for normally distributed continuous variables, or median with interquartile range in the case of skewed distribution. An intention-to-treat analysis will be performed on all randomized subjects to provide unbiased comparisons among groups and avoid the effects of dropout. Study outcomes will be measured as changes from baseline to all assessment points (6-, 12-, 18-month). Changes will be tested with linear mixed models, which account for repeated measures collected in a longitudinal design and deal better with dropouts, without the need for imputation of missing data. Intraclass correlations coefficients will be also reported to take into account the potential correlation among individuals within group. Statistical analyses will be performed with IBM SPSS Statistics.

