### Sample size

The sample size is based on the number of participants needed to detect significant longitudinal changes in PA level. With a statistical power of 0.80, an alpha value of 0.05, a moderate correlation (*r* = 0.5) between measures, and an expected 10% attrition, a total sample size of 180 participants (60 per group) is required to detect a medium effect size (*d* = 0.53) (21). Calculation was performed by a statistician.

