## Discussion

The ONWARDS study aims to explore longitudinal changes in PA, long-term exercise maintenance, health and implementation outcomes among inactive adults using three different digital interventions for PA promotion, namely an activity tracker with the personalized metric PAI, home-based online training *via* Les Mills+ and peer support *via* a Facebook closed-group. Inactive adults often do not access a training facility or use equipment for home exercise. A control group receiving “standard care” was therefore deemed to be unfair for these individuals. All participants in this study will therefore be provided with at least an activity tracker. The presence of three interventional groups will allow testing of which combination of strategies is more effective in increasing PA levels and maintaining them over the long-term.

Psychological factors, including lack of motivation and lack of skills/knowledge, represent a major barrier to PA (9, 10). Perceived self-efficacy can affect both motivation and actions and is important for lasting changes in PA (47). Other effective behavior change techniques used in mobile apps for PA include goal setting, monitoring and feedback about whether or not one gets enough exercise (13). PAI is personalized metric based on heart rate data which can be used by everyone of all ages and fitness levels. The PAI Health mobile app sets a clear goal, which is to keep a weekly PAI score above 100 for disease prevention and health promotion. Users who struggle with keeping physically active can self-monitor their PA level *via* the PAI Health app, which provides a daily feedback on their current PAI score and reminds them to try to reach their goal. Thanks to these features, we expect that the participants in this study will increase their perceived self-efficacy, competence and motivation for exercise which, in turn, might result in higher PA levels and better adherence to PA recommendation.

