Geographical isolation and related environmental factors (e.g., lack of facilities) are especially related to health disparities and inequality in PA (48). Access to training facilities can promote PA with equipment for strength and aerobic exercise as well as group-based classes, which are motivating and result in better long-term adherence (29). However, many people do not have access to these facilities, and others have concerns about their appearance (10). Adverse weather conditions represent another major barrier to participation in PA, and high or low temperatures, rain, snow or wind may all decrease the pleasure derived from outdoor activities (49). Lack of time is one of the most reported reasons why healthy adults do not participate in sport or physical recreation (10, 50). Northern Norway, where this study will be conducted, is a region characterized by frequent adverse weather conditions as well as a high peripherality, with several people living outside urban areas and without easy access to training facilities. Moreover, study participants will be inactive young or middle aged adults, which most likely will be studying or working and might therefore perceive lack of time as a barrier to PA. The possibility for participants in groups B and C to exercise conveniently from home supported by video programmes has the potential to empowering them to perform regular PA while addressing common issues such as lack of time or concerns about appearance. Moreover, interventions with a group atmosphere, such as Les Mills+ online programmes, can be more effective in increasing engagement over time and reducing perceived stress (20).

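### Hypothesis 1, that the tracker with PAI promotes activity, has no randomised test because all three groups receive the tracker; only uncontrolled change from baseline bears on it

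*Protocol article*

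**What the plan says.** Under Study objectives and hypotheses, the article lists three hypotheses. The first concerns the tracker itself: "We hypothesize that the use of activity trackers with the personalized metric PAI can promote PA and improve health outcomes". The second is that adding home-based online training does more. The third is that adding peer support improves long-term adherence. The primary objective is to find which combination of interventions is more effective.

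On who gets the tracker, the section Activity tracker With PAI app says: "Participants in groups A, B and C will be provided with an activity tracker". The Discussion explains that a standard-care control was considered unfair and concludes: "All participants in this study will therefore be provided with at least an activity tracker". The tracker does not come alone: "All participants will also receive information on recommendations for PA, together with a 6-week acclimatization programme".

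Under Statistical analysis, outcomes are expressed as changes from baseline at 6, 12 and 18 months, and "Changes will be tested with linear mixed models". The same section says the intention-to-treat analysis is meant to give unbiased comparisons between the groups. Under Sample size: "The sample size is based on the number of participants needed to detect significant longitudinal changes in PA level".

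**The concern.** A hypothesis that the tracker promotes activity needs a comparison between people with and without it. Here every participant has it from the start of follow-up, so its effect cannot be separated from the passage of time or from anything else given to everyone.

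What remains is change from baseline, and three other things can move it:

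- **Co-intervention.** Activity advice and the 6-week programme are given to all groups together with the tracker. This is certain from the text.
- **Regression to the mean.** Eligibility requires low activity over the last 3 months (Eligibility criteria), so some rise can be expected without any effect. Its size is unknown.
- **Season.** The 6- and 18-month wear periods fall half a year out of phase with baseline. Of weather in general the Discussion says: "Adverse weather conditions represent another major barrier to participation in PA". The article gives neither the size nor the direction of a seasonal difference.

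At stake is what the trial may conclude about one of its three stated hypotheses. The Discussion discloses and justifies the lack of a control group, but it neither withdraws the causal wording nor limits how a within-group rise may be read.

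**Working it through.** **1. What the randomised contrasts isolate** (Study design)

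| Contrast | Differs by | Bears on |
|---|---|---|
| B-A | online training | hypothesis 2 |
| C-B | peer support | hypothesis 3 |
| C-A | both | primary objective (which combination) |
| none | tracker | hypothesis 1 |

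The tracker indicator equals 1 in all three groups, so it drops out of every between-group difference.

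**2. The plan's own sample size**

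Inputs from Sample size: d = 0.53, power 0.80, alpha 0.05 (two-sided assumed), r = 0.5, 10% attrition, 60 per group. With r = 0.5 the SD of a change equals the raw SD: √(2(1 − 0.5)) = 1.

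- Two-group comparison: n = 2(1.96 + 0.842)² / 0.53² = 15.70 / 0.281 = 55.9, so 56 evaluable per group. Multiplying by 1.1 gives 62; dividing by 0.9 gives 63. With 60 × 0.9 = 54 evaluable, power is 0.79.
- Paired pre-post test within one group: about 30 evaluable.

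The stated 60 is therefore close to a between-group calculation and far from a pre-post one, although the text speaks of longitudinal changes.

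**3. Regression to the mean (assumed inputs)**

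The Introduction says one third of Norwegian adults meet the recommendations. Assume that the least active two thirds are eligible and that activity is normally distributed. The cut-off is z = 0.431, and the selected group lies φ(0.431) / (2/3) = 0.545 population SD below the mean. If the screening measure correlates ρ₁ with baseline activity and ρ₂ with follow-up activity, the expected rise without any effect is (ρ₁ − ρ₂) × 0.545.

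| ρ₁ | ρ₂ | Spurious rise (SD) | Share of 0.53 |
|---|---|---|---|
| 1 (selection on the outcome itself) | 0.5 | 0.27 | 51% |
| 0.5 | 0.25 | 0.14 | 26% |
| 0.3 | 0.15 | 0.08 | 15% |
| 0.3 | 0.3 | 0 | 0% |

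The top row is an upper bound. Recruitment and study procedures says eligibility answers are self-reported, whereas the outcome comes from a separate accelerometer recording.

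**4. How often a non-tracker shift would look significant**

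Paired t-test, two-sided 0.05, SD of change = 1, with 54 evaluable in group A or 3 × 54 = 162 pooled. The shifts are assumptions.

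| Shift (SD) | Group A | Pooled |
|---|---|---|
| 0.1 | 0.11 | 0.24 |
| 0.2 | 0.30 | 0.72 |
| 0.3 | 0.58 | 0.97 |

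**5. Season**

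Only the 12-month visit is a whole year from baseline. If enrolment falls in one season, any seasonal difference passes in full into the 6- and 18-month changes. If enrolment is spread over the year, it largely averages out. Recruitment timing is not given.

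A calendar-month covariate does not rescue the first case. Season would then be fixed by visit (0 and 12 months against 6 and 18), so the model could not tell season from time.

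**The case against.** The strongest reply is that this is a disclosed choice outside the primary objective. The Discussion says why there is no untreated group, the stated purpose of three groups is to compare combinations, and the article elsewhere describes its aim as exploring longitudinal change. On this view the defect is one sentence. Much of that stands: the design is legitimate for its primary objective, and the remedy is mainly wording. But disclosing that there is no control does not make a causal hypothesis testable.

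A reader might also infer more than the article supports:

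- **That the whole trial is reduced to pre-post comparison.** It is not. Statistical analysis also plans comparisons between groups, and 60 per group fits a two-group calculation.
- **That regression to the mean accounts for half the design effect.** That needs selection on the accelerometer outcome itself, whereas screening is by self-report.
- **That a biased significant result is likely because a pre-post test has high power.** Power is 0.97 for a change of 0.53 SD with 54 evaluable, but that is not the chance of a false signal. The chance depends on the unknown shift, as tabulated in the working.
- **That season spoils every time point.** The 12-month change is roughly season-matched.
- **That national roll-out would rest on the tracker's pre-post change.** The Discussion makes roll-out conditional on effectiveness, and its surrounding text, on home delivery as an alternative to training facilities, fits online training better. Online training has a randomised contrast.

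**Conclusion.** Hypothesis 1 is wrong as written: it claims an effect of the tracker that the design cannot test. This follows from the allocation alone and rests on no numerical assumption. The bundling with advice and the exercise programme is equally certain, so even a genuine rise caused by the package could not be attributed to the tracker.

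The other two contributions are possible but not established. Regression to the mean ranges from 0 to 0.27 SD, assuming that the least active two thirds are selected and using the correlations shown; self-reported screening points to the low end. A seasonal contribution at 6 and 18 months is an assumption in both size and recruitment timing.

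The point is confined to hypothesis 1. The primary objective and hypotheses 2 and 3 keep their randomised contrasts.

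**What to change.** 1. Reword hypothesis 1 as descriptive: within-group change in activity and health outcomes among users of the whole tracker package (tracker, activity advice and 6-week programme), not attributable to the tracker.
2. Label all within-group changes from baseline as uncontrolled.
3. Rest effectiveness conclusions on the randomised contrasts B-A, C-B and C-A.
4. Present the 12-month change as the roughly season-matched within-group figure, still uncontrolled.
5. Do not rely on a calendar-month covariate to rescue the pre-post change; it helps only if enrolment spans seasons.

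The sample size stays at 180. The cost is wording and a more modest claim for the tracker. For comparison, keeping hypothesis 1 as a randomised test would need a fourth group without the tracker: 4 × 60 = 240 at the planned group size, or 4 × 63 = 252 with 56 evaluable per group and full allowance for 10% attrition. It would also need an untreated group, and the article rejects a standard-care control as unfair.

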### Outcome measures

The primary outcome is the average time spent in moderate and vigorous PA. Objective measurement of PA will be undertaken using the ActiGraph GT3X+ accelerometer worn at the right hip by each participant for eight consecutive days. The ActiGraph GT3X+ should be taken off when showering or bathing. A day of data will be included if there are at least 10 h of data. A minimum of four valid days of data will be required (36). Total physical activity will be measured as total acceleration counts per minute in triaxal vector magnitude (square root of the summed activity counts from all three axes) counts per minute. The intensity of PA will be split by acceleration cut-off of <150 triaxial counts per minute (sedentary time), 150–2,689 triaxial counts per minute for light and >2,690 triaxial counts per minute for moderate and vigorous PA (37, 38), which are calibrated to correspond to <1.5, 1.5–2.9 and 3.0 metabolic equivalents of tasks (METs).

The proportion of participants reaching the recommendation for PA will be measured, for each group, at all time points (Table 1). Longitudinal changes will express a measure of maintenance of long-term adherence to exercise. The proportion of participants reaching the goal of 100 PAI/week will also be measured for the entire duration of the study.

**Table 1 T1:** Schedule of enrolment, interventions, and assessments.

**Time point**	**Enrolment**	**Baseline**	**6-month**	**12-month**	**18-month**
**Enrolment**
Eligibility criteria	X				
Informed consent	X				
Allocation		X			
**Interventions**
Group A					
Group B					
Group C					
**Assessments**
Demographic data		X			
Physical activity level		X	X	X	X
Adherence to PA recommendation		X	X	X	X
Physical fitness (VO_2max_)		X	X	X	X
BMI		X	X	X	X
Waist circumference		X	X	X	X
Quality of life (SF-12)		X	X	X	X
Perceived competence for exercise (PCS)		X	X	X	X
Self-efficacy for exercise (SEE)		X	X	X	X
Social Support (SSES)		X	X	X	X
Reasons for performing physical activity		X	X	X	X
Usability (SUS)			X		
Users' perspectives (interviews)			X		X

*PA, physical activity; VO*_2*max*_*, maximal oxygen uptake; BMI, body mass index; SF-12, 12-Item Short Form Survey; PCS, perceived competence scale; SEE, Self-Efficacy for Exercise Scale; SSES, Social Support and Exercise Survey; SUS, System Usability Scale*.

The maximal oxygen uptake (VO_2max_) is the most precise measure of cardiovascular fitness and represents the body's capacity to transport and use oxygen during exercise. In this study, VO_2max_ will be estimated from a validated non-exercise prediction model which includes age, waist circumference, resting heart rate and leisure-time PA (39, 40). The algorithm used to estimate cardiorespiratory fitness is also integrated and freely available in a publicly accessible online tool (www.worldfitnesslevel.org). One of the co-authors ([name]) holds the Intellectual Property rights for this tool, which is available for commercial actors upon license agreements.

Cardiovascular risk will be assessed by the following risk factors: smoking, body mass index (BMI), and waist circumference. Height, weight and waist circumference will be self-measured by participants and self-reported on the online study questionnaires.

Quality of life will be measured with the 12-Item Short Form Survey (SF-12) (41). Perceived competence will be measured with the perceived competence scale (PCS) for regular physical exercise (42). Self-efficacy will be measured with the Self-Efficacy for Exercise Scale (SEE) (43). Social support for PA from friends and family will measured using the Social Support and Exercise Survey (SSES) (44). Usability of the interventions will be assessed at 6-month only with the System Usability Scale (SUS) (45). Reasons for performing and not performing physical activity will be collected with multiple-choice questionnaires previously used in Norwegian surveys (7).

Users' perspectives will be explored with semi-structured interviews conducted in a subsample of participants at 6- and 18-month to explore their perception on implementation outcomes including adoption, acceptability, adherence and sustainability of the interventions (46). Interviews will be recorded on audio digital file, transcribed verbatim and analyzed *via* Nvivo upon the theoretical frame of the learning theory.

